## Abstract

**Background:**

Transition of care (TOC) is a high-risk period for medication errors as patients move between multiple health care professionals, settings, and changing medication regimens. Ineffective communication systems further increase the likelihood of medication harm and hospital readmission. A TOC service with tailored, patient-specific support may help reduce these risks. Cardiovascular medicines significantly contribute to medication harm, and patients recovering from acute myocardial infarction (AMI) or cardiothoracic surgery (CS) are vulnerable due to complex regimens and frequent medication changes. Pharmacists, as medication experts embedded within cardiology teams, are well positioned to support these high-risk patients, facilitate safer transitions from hospital to home, and provide coordinated postdischarge follow-up.

**Objective:**

This study aims to evaluate the impact of a pharmacist-led interdisciplinary TOC service on reducing medication harm for cardiology patients post-AMI or CS.

**Methods:**

The study will be conducted in two phases: phase 1—intervention development will combine scoping review findings with stakeholder input to design an evidence-based, cocreated, culturally relevant intervention, underpinned by implementation science. A risk prediction model will be developed and validated to identify AMI/CS patients at high risk of medication-related unplanned readmission within 30 days. Phase 2: the RECARD (Reduce Hospital Readmissions for High-Risk Cardiology Patients) trial will use a pre-post design across 3 Australian tertiary hospitals (2 metropolitan and 1 regional) to compare a retrospective usual care patient cohort (referred to as “pre”) with a different prospective patient cohort (referred to as “post”) that includes both usual care and intervention AMI/CS patients receiving the TOC service. Only high-risk poststudy patients will receive the intervention TOC service, consisting of an individualized bundle of TOC activities to optimize medication management, while the remaining poststudy patients will receive usual care. A unique feature of the service is its capacity for hospital clinicians to conduct postdischarge home visits for patients needing additional support. The primary outcome for this study is medication-related 30-day hospital readmission. The analysis will consist of multivariable logistic regression. An economic analysis will be conducted to evaluate the costs associated with the intervention and medication-related readmissions. A comprehensive process evaluation will be conducted using the RE-AIM (Reach, Effectiveness, Adoption, Implementation, and Maintenance) framework to enable learnings from the trial to inform sustainable improvements in this field. A patient survey will be administered at the end of the trial to assess patient experience and elicit patient preferences using a discrete choice experiment.

**Results:**

The predata are currently being collected for patients discharged from the 3 hospital sites during the 12-month prestudy period. The postdata intervention began on December 10, 2025. As of May 27, 2026, a total of 343 patients have been recruited at the 3 study sites.

**Conclusions:**

The findings of this study will inform future implementation of a sustainable cardiac TOC model within the Australian health care setting.

## Introduction

### Background

The transition from hospital to primary care is a high-risk period for patients due to complex communication among multiple health care professionals, frequent medication changes, and complex care plans [1]. These factors increase the likelihood of medication harm and hospital readmission [2]. Implementing a structured transition of care (TOC) service with tailored support may help mitigate these risks [3,4].

Cardiovascular disease remains one of the leading causes of mortality in Australia and is managed with high-risk medications, such as anticoagulants and antiplatelets, that require careful titration [5,6]. These medications are a major contributor to medication harm, leading to medication-related hospital readmissions, morbidity, and mortality [5]. Associated complications include bleeding, acute kidney injury, hypotension-related falls, and electrolyte disturbances. Patients recovering from acute myocardial infarction (AMI) or cardiothoracic surgery (CS) are particularly vulnerable [6,7]. A previous study by the authors found that 6% (94/1564) of post–myocardial infarction patients were readmitted due to severe medication harm [5]. Another Australian study reported that 93% of cardiology unit discharges involved at least one medication-related problem, often linked to uncertainty about medications, drug interactions, and adverse effects [8].

Health inequities further exacerbate adverse cardiovascular outcomes. A dedicated TOC practitioner, trained in medication management, who can advocate for and provide timely navigation for patients as they return to the community remains a significant gap for some of these specialized high-risk patient groups [9]. For instance, in Queensland, hospital programs such as Better Cardiac Care for Aboriginal and Torres Strait Islander teams have improved aspects of medication management, such as ensuring medication supply and improving discharge communication [7,10-13]. Systemic inequities, treatment complexity, and limited access to culturally safe or patient-tailored services likely heighten risks, necessitating tailored, co-designed TOC interventions, as we propose.

Current health care systems are not adequately designed to support patients postdischarge, highlighting the need for a multifaceted approach to improve medication management at TOC [14]. Postdischarge care is often hindered by inadequate communication channels, a lack of early engagement with patients and carers, and difficulty scheduling follow-up with general practitioners (GPs) [15]. Up to 50% of patients lack a regular GP or community pharmacist, which further compromises continuity of care [15]. Given the medication burden and complex health care needs of the post-AMI and CS population, a formal TOC approach with a pharmacist leading an interdisciplinary team is vital to improving outcomes and reducing readmissions. Pharmacist-led TOC services have been shown to reduce readmissions and medication harm while maximizing quality of life for cardiovascular patients [2]. A hospital-initiated, pharmacist-led multidisciplinary approach facilitates improved medication management by encouraging patient and caregiver engagement, development of shared care plans, and collaboration with health care professionals [16]. While existing programs address heart failure and cardiac rehabilitation [17], no dedicated initiatives focus on postdischarge medication management for high-risk patients following an AMI or CS event.

Community-based medication review programs, such as Home Medication Reviews and Residential Medication Management Reviews, provide some support but are not tailored for patients recently discharged after an AMI or CS [18]. These programs are also underutilized by Aboriginal and Torres Strait Islander peoples and those in rural and remote areas and are not always available in a timely manner for immediate postdischarge care [9]. The current TOC model relies heavily on written communication to GPs, which may not be received in time for actions to be taken and is not consistently shared with community pharmacists for their active clinical involvement [19]. Geographic barriers and limited health care access further hinder timely follow-up, increasing the risk of medication harm. The members of a TOC team can act as patient advocates, ensuring effective communication and timely care coordination postdischarge. Pharmacists are uniquely positioned to perform this role for high-risk patients due to the medication misadventure risks they face during TOC.

The TOC service to RECARD (Reduce Hospital Readmissions for High-Risk Cardiology Patients) patients is a program that will codevelop, implement, and evaluate a patient-centered, pharmacist-led, interdisciplinary TOC service to reduce medication-related hospital readmissions in patients following AMI and CS. There is no existing evidence-based framework that systematically addresses medication harm at TOC for this cohort. There is an urgent need for a structured, patient- and team-centered TOC model that proactively identifies high-risk patients, engages them to co-design their care plans, ensures seamless communication among health care providers, and provides a home-based visit. This approach will integrate pharmacists into TOC teams that include nurses and Indigenous health workers to provide timely medication management support and improve patient outcomes.

### Trial Hypothesis

Compared with usual care, the implementation of the interdisciplinary pharmacist-led TOC intervention will result in a significant reduction in 30-day medication-related hospital readmissions, be positively received by patients, and be cost-effective.

### Aim

To evaluate the effectiveness of a pharmacist-led interdisciplinary TOC service in reducing medication-related hospital readmissions among cardiology patients following acute AMI or CS.

### Study Objectives

#### Primary Objective

The primary objective is to determine if an interdisciplinary pharmacist-led cardiology TOC service reduces the rate of 30-day medication-related hospital readmissions compared with usual care.

#### Secondary Objective

The secondary objective is to evaluate the impact of the TOC service based on key domains of the RE-AIM (Reach, Effectiveness, Adoption, Implementation, and Maintenance) framework [20], including the following:

Reach: The target population by the absolute number, proportion, and representativeness of patients who are willing to participate in the RECARD TOC service.Proportion of patients who engage with the TOC service: The proportion of patients who consent to and engage with the TOC service, compared with the broader population of patients with AMI/CS and the high-risk patients across the sites (Princess Alexandra Hospital [PAH], Royal Brisbane and Women's Hospital [RBWH], and Townsville University Hospital [TUH]).Effectiveness: The impact of the TOC service on secondary outcomes, including clinical effects, potential negative effects, and economic outcomes.30-day all-cause readmissions: All patients who are readmitted to the hospital for any presentation or reason within 30 days.60-day all-cause readmissions: All patients who are readmitted to the hospital for any presentation or reason within 60 days.90-day all-cause readmissions: All patients who are readmitted to the hospital for any presentation or reason within 90 days.Subanalysis of the primary outcome by cohort: 30-day medication-related readmission subanalysis for post-AMI patients and CS patients as subgroups.Subanalysis of the primary outcome by site: 30-day medication-related readmission for metropolitan versus regional sites.Subanalysis of the primary outcome by intervention: 30-day medication-related readmission for high-risk patients who received the intervention (TOC service) and those who did not, as subgroups.Preventable harm: Preventability of 30-day medication-related readmissions as assessed through the modified Schumock and Thornton criteria [21].Severity of harm: Severity of 30-day medication-related readmissions as defined through severity definitions by Morimoto et al [22].Patient experience: Patient experience and preferences assessed through a survey.Cost-effectiveness: Economic evaluation to assess the cost per readmission avoided.Adoption: The target staff, settings, systems, and communities by the absolute number, proportion, and representativeness of settings and staff willing to initiate and deliver the TOC service.TOC staff field notes during service delivery: TOC service staff (ie, TOC pharmacist, TOC nurse, or Indigenous health care worker) notes on their experiences with delivering the service to post-AMI/CS patients.Postimplementation interviews with TOC staff: Interviews undertaken with TOC service staff to determine their adoption of the service and willingness to deliver the service to patients.Implementation: Consistency, costs, and adaptations made during the delivery of the TOC service, both at the setting and individual levels.Communication outcome (discharge summary): Number of discharge summaries provided to primary care providers.Communication outcome (home visits): Number of follow-up home visit consultations provided within the TOC service.Process outcome (adaptations to the TOC service): Adaptations made to the TOC service by TOC staff during the study, as indicated through the delivery of activities in the TOC bundle and relevant notes during service delivery.Maintenance (and Sustainability): Long-term cost-effectiveness and local policy and procedure development.Economic sustainability: Sustainability of the intervention in the long-term based on the cost-effectiveness data.Local policy and procedures: Local policies and procedures have been developed during the pilot that will support long-term sustainable adoption of the TOC model.

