###### Methods

The model will be developed and validated using pretrial data from 1 to 2 Queensland hospitals. One thousand patients with a primary diagnosis of AMI and/or CS admitted to the PAH or TUH from July 2023 to June 2024 will be included in the model development study. Learnings from the development of a prior risk prediction model for medication harm [28] will be used to inform the new risk model.

Data will be collected from digital systems on patient characteristics, comorbidities, length of hospital stay, clinical parameters, and reason for admission. Other clinically relevant criteria not currently known will be identified through our consolidation of the literature [1] and data from part A.

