### Precohort

All patients admitted to the study sites with an index admission for AMI or CS between July 1, 2023, and June 30, 2024, will be included. A waiver of consent has been granted to collect these retrospective data for the historical usual care control group.

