### Participant Identification, Recruitment, and Consent

Patients in the prestudy cohort will be retrospectively identified using the Health Information Management System reporting information and *International Statistical Classification of Diseases and Related Health Problems, Tenth Revision* (*ICD-10*; or equivalent) data. In contrast, patients in the postcohort will be identified through the presenting diagnosis (AMI or CS) or through a confirmed diagnosis on completed angiograms as per clinical records.

In the poststudy cohort, only patients identified as high-risk of readmission, either by the risk prediction model or by referral from the treating team, will be offered the TOC service model. Patients who are not identified as high-risk will receive usual care.

Patient recruitment will be completed by the TOC pharmacist or a member of the research team after patient identification by a member of either the TOC team, the research team, or the local treating team.

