### Statistical Analysis

An intention-to-treat analysis will be conducted. Participants who are lost to follow-up (ie, participants who do not complete the intervention, withdraw consent, or die during the study) will be included in the intention-to-treat analysis for the primary outcome. Participant characteristics will be summarized according to the prestudy and poststudy cohorts. Characteristics will be summarized and presented descriptively using mean (SD), median (IQR), and n (%), as required. Independent *t* tests and chi-square tests will be undertaken to determine whether there are any differences in baseline characteristics between the prestudy and intervention cohorts.

The primary outcome is a comparison of 30-day medication-related hospital readmissions in the prestudy cohort compared with the poststudy cohort. Secondary outcomes will be compared similarly. The analysis will consist of multivariable logistic regression. The explanatory variables will consist of a variable indicating the study period along with any relevant potential confounding variables we wish to control for (eg, patient age, sex, etc). The results for these outcomes will be considered significant at the 5% level, with 95% CIs reported. Subgroup analysis will also be undertaken to assess whether the clinical impact of the intervention varied by location (regional vs metropolitan sites), Indigenous and non-Indigenous patients, and high-risk patients identified according to the model of treating team referral.

Evaluation will be conducted using the RE-AIM framework as described earlier [20]. Data will be analyzed descriptively, and other metrics (eg, primary outcome) will be mapped as calculated above or informed by the patient survey and economic analysis.

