#### Informed Consent

Participants recruited to the TOC service in the prospective cohort of the trial (phase 2) will be provided with information about the trial and will need to provide written or verbal consent prior to receiving any intervention.

Consent for publication will also be obtained from these study participants, which will include consent to publish aggregated deidentified data in a relevant medical journal.

Consent for the remaining participants in the prospective and retrospective cohorts of the RECARD trial (phase 2), who receive usual care, is covered by Public Health Act (PHA) approvals from the Queensland Government (PHA 107694 and PHA 109242).

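### The high-risk subanalysis groups patients by receipt of the service, which is an as-treated contrast; group them by model flag at the index admission, and keep the referral route descriptive

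*Protocol article*

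**What the plan says.** Under Secondary Objective (Effectiveness), one subanalysis of the primary outcome is "30-day medication-related readmission for high-risk patients who received the intervention (TOC service) and those who did not, as subgroups". The grouping variable is receipt.

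Participant Identification, Recruitment, and Consent says who is offered the service: "only patients identified as high-risk of readmission, either by the risk prediction model or by referral from the treating team". It adds: "Patients who are not identified as high-risk will receive usual care". The Phase 2 overview and Usual Care agree. Under Informed Consent, patients recruited to the service "will need to provide written or verbal consent prior to receiving any intervention".

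Statistical Analysis states: "An intention-to-treat analysis will be conducted". It defines the primary contrast by study period and compares secondary outcomes in a similar way. It also plans a subgroup analysis of "high-risk patients identified according to the model of treating team referral", which I read as identification by the model or by treating-team referral.

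The risk model (Phase 1 Part B, Methods) is developed on "One thousand patients with a primary diagnosis of AMI and/or CS admitted to the PAH or TUH from July 2023 to June 2024", with 30-day medication-related readmission as its outcome. The precohort is "All patients admitted to the study sites with an index admission for AMI or CS between July 1, 2023, and June 30, 2024".

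**The concern.** The trial expects benefit only in the high-risk patients, so readers will turn to this subanalysis, particularly if the whole-cohort result is null. Its comparator is not defined, and each possible reading has a problem.

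- **Postcohort non-receivers.** The design has no high-risk usual-care group in the post period. Those who did not receive the service are a remainder formed by refusal, missed identification or lack of capacity. The service also runs over the same 30 days as the outcome, so a definition of receipt that needs a postdischarge contact would place early readmissions among the non-receivers.
- **Precohort high-risk patients.** The model that would flag them was to be developed on admissions from the same window, at two of the three sites, with the same outcome. Flags given in-sample pick out patients partly because they had the event.
- **Referred patients.** Referral is a prospective clinical judgment. Nothing comparable is described for the precohort.

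**Working it through.** **1. The plan's own figure.** Sample Size gives 7% versus 4.9%, significance level .05 (two-sided assumed) and power 0.80.

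n = [1.960·√(2·0.0595·0.9405) + 0.842·√(0.07·0.93 + 0.049·0.951)]² / 0.021² ≈ 1991 per period

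The protocol states 1990, so the figure reproduces. 1990/0.9 = 2211, and 35% of 2211 = 774 (stated as about 775). The present point does not touch this calculation.

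**2. Who the postcohort non-receivers are.** About 775 patients are expected to be flagged, to consent and to be treated. If a share r of flagged patients declines or is missed (the documents give no r), non-receivers number 775/(1−r) − 775.

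| r (assumed) | Non-receivers | Power, 12% vs 6% | Power, 10% vs 7% |
|---|---|---|---|
| 10% | 86 | 55% | 20% |
| 20% | 194 | 78% | 31% |
| 30% | 332 | 90% | 40% |

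These powers ignore selection bias.

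**3. Immortal time.** Assumptions: 14% 30-day risk in flagged patients, constant hazard, 10-30% decline, no true effect. The daily hazard is λ = −ln(0.86)/30 = 0.00503. Let t be the day that must be reached to count as having received the service, and d the share declining.

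- Event before t: F = 1 − e^(−λt)
- Risk in receivers: 1 − e^(−λ(30−t))
- Risk in non-receivers: [0.14d + (1−d)F] / [d + (1−d)F]

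| Receipt means | F | Receivers | Non-receivers (d = 30% to 10%) | Apparent risk ratio |
|---|---|---|---|---|
| In-hospital activity (t = 0) | 0 | 14.0% | 14.0% | 1.0 |
| Day-3 contact | 1.5% | 12.7% | 16.9% to 24.2% | 0.75 to 0.52 |
| Day-14 consult | 6.8% | 7.7% | 25.8% to 46.6% | 0.30 to 0.17 |

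By day 14, 0.068/0.14 = 48.5% of events have occurred. Days 3 and 14 are the postdischarge contacts in Table 1.

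**4. Precohort flagged by the model.** Maximum overlap is 1000/2211 = 45%. Optimism was simulated with 1000 development patients, a 7% event rate, the top 25% flagged, no treatment effect, independent normal predictors with assumed log odds ratios of 0.25 or 0.35 per SD, 300 repeats and 20,000 new patients per repeat.

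| Model | Flagged rate, development | Flagged rate, new | False fall (points) | × 45% |
|---|---|---|---|---|
| 4 fixed predictors | 14.0% | 13.2% | 0.8 | 0.4 |
| 8 fixed, all informative | 14.3% | 12.9% | 1.4 | 0.6 |
| 8 fixed, 4 informative | 14.4% | 12.8% | 1.6 | 0.7 |
| 8 screened from 20 | 14.9% | 12.2% | 2.7 | 1.2 |
| 8 screened from 30 | 15.5% | 11.8% | 3.7 | 1.7 |

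For scale, a 2.1-point overall reduction confined to 35% of patients needs 0.021/0.35 = 6.0 points among the high-risk.

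**5. Referral.** Sample Size expects 25% flagged by the model and a further 10% referred, so 10/35 = 29% of treated patients enter by a route with no described precohort equivalent.

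**The case against.** The item is listed as a subanalysis of the primary outcome, and the primary outcome is under intention to treat, which expressly keeps patients who do not complete the intervention. RE-AIM data are to be analysed descriptively, and this item sits under RE-AIM Effectiveness. Figure 2, which sets out who receives what, is not shown, and a statistical analysis plan may settle the scoring of a historical comparator. This is fair as to detail. It does not remove the difficulty that the stated grouping is by receipt, in a design that leaves no high-risk usual-care group in the post period.

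A reader might infer more than the documents support, in four ways:

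- **That no valid comparator exists.** For the model route one does: RBWH precohort patients, and PAH/TUH patients not used in development, are out of sample.
- **That every reading manufactures benefit.** Decliners may be sicker or healthier, and missed patients may be low-risk short stays. The direction is unknown.
- **That a risk ratio of 0.17-0.30 is the expected bias.** It holds only if receipt means reaching day 14. Consent and many activities take place during admission, and an in-hospital definition gives 1.0.
- **That the upper optimism figures apply.** They rest on univariable screening from many candidates. The protocol uses univariable regression to assess viability and selects by penalized regression or clinical relevance.

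The documents also never say that precohort patients will be scored, so that part of the point is conditional.

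**Conclusion.** The point holds in limited form. Read within the postcohort, the planned receipt contrast is as-treated, of uncertain bias direction, and at odds with the stated intention-to-treat principle. Immortal time is an extra bias whose size runs from none to severe depending on a definition of receipt that the protocol does not give; the ratios in the working rest on an assumed 14% risk and assumed refusal rates. If flagged precohort patients are the comparator and are scored in-sample, their event rate is overstated by about 0.4-0.7 points overall with 4-8 fixed predictors, and by more with heavy screening. Against the 6.0 points needed in the high-risk group, 0.4-0.7 is modest but not negligible. It assumes full overlap of the 1000 development patients with the precohort, and assumed predictor strengths. A pre-post effect in referred patients cannot be estimated from what is described. A reader might extend the criticism to the primary result, but that comparison uses whole cohorts by period, does not depend on flags or receipt, and is unaffected.

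**What to change.** Replace the receipt contrast with model-flagged post versus model-flagged pre patients. Group by flag at the index admission, regardless of uptake or completion, with one frozen model and cut-off applied to both periods. For precohort patients used in development, assign the flag from out-of-fold predictions; the planned cross-validation covers performance metrics only. Add a sensitivity analysis that excludes development patients. Report referral-only patients, and received versus not received, descriptively and without an effect claim.

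The cost is revised wording and re-scoring of up to 1000 records. Scoring looks feasible, since Postcohort (Prospective Data Collection) says that the same variables are collected in both periods. The exclusion analysis has a real downside: the precohort shrinks and its case mix shifts, because RBWH contributes no CS patients, so it should adjust for AMI/CS and site. The team should also confirm that the consent waiver for usual-care patients covers flagged patients who decline the service, since this grouping needs their readmission data. According to Results, no preliminary analysis has been undertaken and analysis is planned for January to March 2027, so the change can still be made before any outcome is analysed.
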